### Consent and Recruitment

Based on local expertise on school student numbers in each country, approximately 6 schools will be selected in each country to achieve a total sample size of 228 per country. Prospective schools will be selected in consultation with the local departments of education. Once schools are identified, permission to conduct the study will be sought from the principal of each selected school. Teachers and parents or legal guardians of prospective participants will then receive an information sheet outlining the procedure and purpose of the study and contact information, and a consent form. On receiving the written parental or guardian consent, the aims, process, and outcome of study will be explained to prospective student participants and their written assent will be sought. Only schoolchildren who have provided informed assent and parental consent will be included in the study. Teachers and parents will be recruited a month before follow-up. As part of the recruitment process, an information sheet will be provided and informed consent will be sought. Once written consent is obtained, teachers and parents will be recruited into the study.

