### Randomization

Schools within each country will be randomly allocated to control or intervention arm using Microsoft excel (Microsoft 365) RAND function. Allocation will remain for the duration of the project.

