### Data Analysis

#### Quantitative

Descriptive statistics will be computed to ascertain variable distributions.

Normality of distribution will be checked using the Shapiro-Wilk test, with significance set to *P<*.05 (2-sided). In acceptability analyses, negatively worded statements will be reverse scored to align the direction of the scale. Spearman correlation coefficient will be used to assess criterion validity among different questionnaire items. Exploratory factor analysis with oblique rotation will then be performed to assess construct validity. The primary outcome of the study is KAP scores for OV and STH.

OV and STH KAP scores will be analyzed separately. KAP scores for each questionnaire will be developed by calculating the total points for knowledge, attitude, and behavior for each student and expressed as a percentage score. Changes in self-reported KAP scores will be analyzed using linear regression. To assess the differences in KAP between control and intervention schools at baseline and follow-up, generalized-estimating equation models will be used to account for clustering within schools and repeated KAP assessment for participants. Potential confounders including age and sex will be incorporated in the model. Spearman correlation coefficient will be used to estimate correlations among acceptability, knowledge, attitudes, and self-reported behavior. Chi-square tests will also be used to measure associations between KAP and acceptability.

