### Power

The sample size was calculated to achieve 80% power, assuming baseline knowledge of 30 percentage points (as reported in the original “Magic Glasses” intervention by Bieri et al [31]) and a design effect of 2 to account for cluster sampling. Accounting for 10% attrition, it was estimated that a total of 227 participants would be needed to detect a difference of 5 percentage points in knowledge between intervention and control groups. As such, we will aim to enroll a total of 228 schoolchildren in years 3-5 (114 in intervention arm, 114 in control arm) in each country.

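### GEE is chosen for the primary comparison with only about 6 randomized schools per country and no few-cluster inference named; with its usual large-sample inference the 5% test would run at about 15-19% per country or 7-11% pooled

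*Protocol article*

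**What the plan says.** All places are in the protocol article.

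- **Unit of randomization** (Randomization): "Schools within each country will be randomly allocated to control or intervention arm". Each school is a cluster.
- **Number of clusters** (Consent and Recruitment): "approximately 6 schools will be selected in each country to achieve a total sample size of 228 per country". Over three countries that is about 18 schools.
- **Analysis** (Data Analysis, Quantitative): to compare the arms on KAP at baseline and follow-up, "generalized-estimating equation models will be used to account for clustering within schools and repeated KAP assessment for participants", with adjustment for confounders including age and sex.
- **Sample size** (Power): set for each country separately, with 80% power for a 5-point difference in knowledge and "a design effect of 2 to account for cluster sampling".

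The article names no variance estimator for the GEE, no reference distribution or degrees of freedom, no school-level analysis and no permutation test. It does not say whether the model is fitted within each country or to all three together.

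**The concern.** The sandwich variance in GEE is justified as the number of independent clusters grows. Adding pupils within a school does not help. With few schools two things go wrong. The fitted residuals are too small, which biases the variance downwards. The normal critical value of 1.96 also ignores how poorly a between-school variance is estimated from a handful of schools. Both make p-values too small and intervals too narrow.

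This is the comparison on which effectiveness rests, and the abstract says that the results will inform a scaling-up protocol in three countries. A country-level claim from about 6 schools is the most exposed.

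**Working it through.** **Inputs.** About 6 schools per country and 18 overall (Consent and Recruitment). Randomization of schools within country (Randomization). 228 children per country, so 228/6 = 38 per school, or about 34 after 10% attrition. Design effect 2, which implies an intraclass correlation of about 1/37 = 0.027. *Assumed:* an equal split of schools (3 v 3 per country, 9 v 9 overall) and a two-sided 5% level, which the article attaches only to the normality check.

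**The plan's own figure.** The article gives no error rate for the GEE test. Its stated number is 227 per country, which needs a standard deviation that it does not give. With SD = 9 the usual normal formula gives n per arm = 2 × ((1.960 + 0.842) × 9/5)² = 50.9, so 51. Then 51 × 2 arms × 2 (design effect) = 204, and 204/0.90 = 227. SD = 10 gives 280 and SD = 15 gives 632. So 227 fits SD ≈ 9 with normal quantiles. The error rates below do not depend on the SD.

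**Closed form for equal-sized schools.** Let M be the number of schools and df = M minus the number of school-level parameters. The arm effect is then a difference of school means. With SSE the residual sum of squares of those means:

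- uncorrected sandwich variance = 4 × SSE/M²
- unbiased variance = 4 × (SSE/df)/M
- ratio = df/M

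So the z test at 1.96 rejects when |t_df| > 1.96 × √(df/M). If the software applies an M/(M−1) factor, the threshold is 1.96 × √(df/(M−1)).

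| Analysis | M | df | Threshold | Type I error | With M/(M−1) |
|---|---|---|---|---|---|
| One country | 6 | 4 | 1.600 | 18.5% | 15.4% |
| Pooled, no country terms | 18 | 16 | 1.848 | 8.3% | 7.5% |
| Pooled, country terms | 18 | 14 | 1.729 | 10.6% | 9.7% |

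Removing the variance bias but keeping 1.96 still leaves P(|t₄| > 1.96) = 12.2% for one country and 6.8-7.0% pooled. Both sources therefore need treatment.

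**Interval width.** Compared with a t interval, the uncorrected 95% interval has relative width 1.600/2.776 = 0.58 for one country (42% too narrow), 1.848/2.120 = 0.87 pooled (13% too narrow), and 1.729/2.145 = 0.81 pooled with country terms (19% too narrow).

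**Simulation under no effect.** GEE, exchangeable within school, adjusted for age and sex, 34 children per school. Simulation error is about 0.9 percentage points either way.

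- 6 schools: 18-20% over follow-up-only and arm-by-time models and intraclass correlations of 0.027 and 0.10; 20-24% with unequal school sizes (coefficient of variation 0.4). Model-based standard errors gave about 19%.
- 18 schools with country terms: 10-11% for the follow-up model and 7-8.5% for the arm-by-time model.
- Bias-reduced variance with a t reference: about 3% for 6 and for 18 schools. Bias-reduced variance with a normal reference: about 8.5% for 6 schools.

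**Power cost of a t reference.** Take a design with exactly 80% power under z, so a noncentrality of 1.960 + 0.842 = 2.802. With the same true standard error, t gives about 56% power on 4 df, 74% on 14 df and 75% on 16 df.

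**The case against.** The strongest reply is that the article names a model and not a variance estimator. It nowhere says uncorrected or normal reference. Such details are often left to an analysis plan, and one of the remedies below is itself a GEE. That is fair, and it makes the error rates conditional. It does not remove the point: the article chooses a large-cluster method for a design with very few clusters, and following it with the usual inference gives the wrong error rate.

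Three stronger readings are not supported.

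- *The evidence across the three countries has two to four times its nominal error rate.* Only a single-country analysis approaches that (15.4/5 = 3.1 to 18.5/5 = 3.7). Pooled, 7-11% is about 1.4 to 2.2 times nominal, and the article does not say which analysis is primary. Sizing per country suggests separate analyses but does not settle it.
- *School clustering may drop out because GEE takes one clustering level and the pupil may be used as the subject.* The article states the aim of accounting for clustering within schools. With school as the cluster, repeated measures on a pupil nest inside it.
- *The split is 3 v 3.* The school count is approximate, and the 114 v 114 in the Power section counts children. The equal split is an assumption here.

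It is also right that the remedy costs more than a software option, because the power loss in a country analysis is large.

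**Conclusion.** The point holds in conditional form. If the stated GEE is run with a sandwich variance and a normal reference, the nominal 5% test runs at about 15-19% with 6 schools and about 7-11% with 18. By the closed form the 95% intervals are about 42% too narrow per country and 13-19% too narrow pooled, without an M/(M−1) factor. Every variant checked that keeps the normal reference exceeds 5%. The result rests on about 6 schools per country, an equal split and, for the closed form, equal-sized schools; unequal sizes made the single-country rate worse. The documents do not show that the test will in fact run at these rates, since an analysis plan that is not shown could add a correction. The choice concerns the primary comparison and should be settled before outcome data are compared by arm.

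**What to change.** State whether the primary analysis is pooled or per country, and replace the GEE sentence with one of these:

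1. GEE with school as the cluster, a bias-corrected variance (Mancl-DeRouen, Kauermann-Carroll or Fay-Graubard) and a t reference on schools minus school-level parameters.
2. A linear mixed model with random intercepts for school and, if both waves are modelled, for pupil, with Kenward-Roger or Satterthwaite degrees of freedom.

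Include country terms when pooling. A permutation test over the country-stratified allocations actually possible can support the pooled result. With 3 v 3 in each country there are C(6,3) = 20 allocations per country and 20³ = 8,000 in all. Within one country the smallest two-sided p would be 2/20 = 0.10, so the permutation test is useful only for the pooled comparison.

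**Cost.** No new data. Intervals widen, and bias-corrected GEE with t may be somewhat conservative (about 3% in simulation). A country analysis sized for 80% under z has about 56% on 4 df, so country results should be presented with that limited precision. A pooled design at exactly 80% would fall to about 74-75%. Here the pooled sample of 684 is three times the per-country size, so power for the same 5-point difference starts higher than that.

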The present study is designed to assess the acceptability of 2 new “Magic Glasses” cartoons, developed for the LMB, and their impact on schoolchildren’s self-reported KAP of STH and OV. Several studies have identified acceptability as a key indicator for initial and sustained intervention success [32-36]. However, there remains a lack of consistency among acceptability measures and definitions in public health research. Sekhon et al [37] developed the Theoretical Framework of Acceptability (TFA), and defined acceptability as “a multi-faceted construct that reflects the extent to which people delivering or receiving a healthcare intervention consider it to be appropriate, based on anticipated or experienced cognitive and emotional responses to the intervention” [37]. The TFA outlined 7 domains of acceptability, “affective attitude, burden, perceived effectiveness, ethicality, intervention coherence, opportunity costs, and self-efficacy” [37]. In order to conduct a robust assessment of all the domains of acceptability, the acceptability of the intervention will be assessed using mixed methods. Quantitatively using an adapted version of the TFA questionnaire [38] and qualitatively using focus group discussions (FGDs) with schoolchildren and key informant interviews (KIIs) with teachers. The KAP questionnaire will be administered at baseline and follow-up to assess the impact of the intervention, and the intervention coherence domain of acceptability.

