#### “Magic Glasses Opisthorchiasis” Delivery and Acceptability Assessment

In intervention schools, the OV-baseline KAP assessment and OV intervention will be administered on the same day. Once OV-baseline KAP assessment has been completed, the MGO intervention package will be administered. MGO will be presented to schoolchildren and teachers in their classroom twice. Once the cartoon has been shown, schoolchildren will receive a comic pamphlet with the key messages of the cartoon. A classroom discussion will then be held to go over the messages and clarify any confusion among the students. Following the classroom discussion, an acceptability questionnaire will be administered to assess students’ initial acceptability of the cartoon. As with the KAP assessment, paper questionnaires will be administered in classrooms by research staff and completed by students individually. The acceptability questionnaire will contain multiple-choice and open-ended questions (see Multimedia Appendices 4 and 5). The questionnaire was adapted from the TFA [38] to include age-appropriate language for the schoolchildren, and specific questions on OV. Once the acceptability assessment is completed, the homework drawing competition will be explained: students will be asked to draw warning signs of OV infection, using the messages from the cartoon and comic pamphlet as a guide.

A reinforcement session will be held 6-8 weeks after the first presentation of MGO. The cartoon will be replayed twice to the student cohort, followed by a classroom discussion and explanation of the homework essay competition. Students will be asked to identify people who are at risk of liver fluke infection and write down why they are at risk, and how they can avoid liver flukes.

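### Acceptability and KAP are linked only by unadjusted Spearman and chi-square tests, which can carry pupils' starting KAP and, if countries are pooled, country differences

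*Protocol article*

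**What the plan says.** The Quantitative part of Data Analysis names two analyses for this link: "Spearman correlation coefficient will be used to estimate correlations among acceptability, knowledge, attitudes, and self-reported behavior", and then "Chi-square tests will also be used to measure associations between KAP and acceptability". No covariate is attached to either.

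Covariates appear once: "Potential confounders including age and sex will be incorporated in the model". That sentence directly follows the one on generalized estimating equations for control versus intervention schools, so it belongs to the arm comparison. It names age and sex. It does not name baseline KAP or country.

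KAP is scored as a level, by "calculating the total points for knowledge, attitude, and behavior for each student and expressed as a percentage score". Change is handled in a separate step: "Changes in self-reported KAP scores will be analyzed using linear regression".

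The delivery section for the opisthorchiasis package (MGO) describes intervention schools. Baseline KAP is completed first, the cartoon is shown and discussed on the same day, and then: "Following the classroom discussion, an acceptability questionnaire will be administered to assess students’ initial acceptability of the cartoon". The soil-transmitted helminth package (MGLM) follows the same procedure. KAP is repeated in all schools at about 9 months (Follow-Up).

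**The concern.** Randomisation protects the comparison between arms. It does not protect a comparison between pupils inside the intervention arm who liked the package more or less. A pupil who starts with higher KAP may find the cartoon easier to follow, rate it higher, and also score higher 9 months later. Acceptability and follow-up KAP then correlate even if acceptability has nothing to do with what was learned.

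Country can act in the same way. Each country has its own language version, and mean levels may differ on both scales. Pooling would put those differences into the coefficient, in either direction.

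Both tests also treat pupils as independent, although the Power section assumes a design effect of 2 for cluster sampling.

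What is at stake is a secondary result tied to the article's first aim, acceptability. A significant coefficient could be taken as support for the package when it shows only who knew more at the start.

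**Working it through.** **Plan figures.** The article gives no design figure for this correlation. Its only computed sample size (227 per country, for knowledge between arms) depends on a standard deviation that is not stated, and it does not bear on this point.

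**Inputs from the article**
- Intervention pupils: 114 per country (Power), so 3 × 114 = 342. After 10% attrition: 342 × 0.9 = 308 in all, 114 × 0.9 = 103 per country.
- Schools: about 6 per country (Consent and Recruitment). If split equally, about 3 × 3 = 9 intervention schools.

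**Assumed inputs (not in the article)**
- Correlation of acceptability with baseline KAP: 0.2, 0.3, 0.4.
- Correlation of baseline with follow-up KAP: 0.4, 0.5, 0.6.
- No link between acceptability and follow-up KAP once baseline KAP is known.
- Two-sided 5% test.

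**Artefact from starting KAP.** r = r(acceptability, baseline) × r(baseline, follow-up). With z = atanh(r) × √(n − 3), the chance of p<0.05 is 1 − Φ(1.96 − z) + Φ(−1.96 − z).

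| r | pooled, n = 308 | one country, n = 103 |
|---|---|---|
| 0.2 × 0.4 = 0.08 | z = 1.40, 29% | z = 0.80, 13% |
| 0.3 × 0.5 = 0.15 | z = 2.64, 75% | z = 1.51, 33% |
| 0.4 × 0.6 = 0.24 | z = 4.28, 99% | z = 2.45, 69% |

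**Artefact from country, if pooled.** Take three equal countries with means −s, 0, +s on both scales and within-country SD 1. Then r = (2s²/3) / (1 + 2s²/3).
- s = 0.5: 0.167 / 1.167 = 0.14, significant in about 71% at n = 308.
- s = 1: 0.667 / 1.667 = 0.40.

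**Simulation check.** 3 × 103 = 309 pupils, 1,000 runs per scenario, no effect of acceptability given baseline KAP and country.

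| Scenario | mean raw Spearman | p<0.05 |
|---|---|---|
| neither source | 0.00 | 4.6% |
| baseline only, 0.2 and 0.5 | 0.10 | 41% |
| baseline only, 0.3 and 0.5 | 0.14 | 71% |
| baseline only, 0.4 and 0.6 | 0.23 | 98% |
| country only, s = 0.3 | 0.06 | 16% |
| country only, s = 0.5 | 0.14 | 69% |
| both (0.3 and 0.5; s = 0.3 or 0.5, same direction) | 0.19 to 0.27 | 91% to 99% |
| both (0.3 and 0.5; s = 0.5, opposite directions) | −0.02 | 5.3% |

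The partial Spearman given baseline KAP and country averaged 0.00 to 0.01 in every scenario. Correlating acceptability with the raw change score is no remedy: it gave about −0.10 to −0.17 whenever acceptability correlated with baseline KAP.

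**Clustering.** With neither artefact, but school variance of 0.1 added to a pupil variance of 1 on both scales, the raw test rejected in 7.3% of runs against 4.6% without it. In that setting clustering is the smaller problem.

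The chi-square tests were not simulated. They are open to the same two sources, because they too use no covariates.

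**The case against.** The strongest reply is that a correlation matrix is descriptive and that Spearman estimates it correctly. The coefficient is an artefact only if the target is a link between acceptability and gain in KAP, and the article does not state that target. Most of this stands, and it limits the point in four ways.

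- **Use as impact evidence.** A reader might infer that the coefficient will be presented as showing that accepted means learned. The Background does say "Several studies have identified acceptability as a key indicator for initial and sustained intervention success", but that summarises cited literature and sets no rule for reading this result. Impact is assigned to the KAP comparison between arms. The article also uses KAP to inform acceptability domains such as intervention coherence, for which a level-on-level association is a fair description.
- **Time point.** The article does not say whether KAP here means baseline, follow-up or change. With baseline KAP, the tendency of better-informed pupils to like the package is the quantity estimated and not a bias, but then it says nothing about learning.
- **Pooling.** Nothing says that countries are pooled. Sample size is set per country and allocation is within country. Analysis by country removes the country part and lowers the rejection rates, but the baseline part remains.
- **Size.** Every correlation and country shift above is assumed.

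One could add that a journal article leaves such detail to a full plan. That would cover a silence. Here the article names the two tests, and a better method using data already collected is available.

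**Conclusion.** The concern holds in a conditional form. The only analyses named for acceptability and KAP are unadjusted and ignore schools, on an exposure that is not randomised. If follow-up KAP is used, the coefficient carries starting KAP: about 0.08 to 0.24 under the assumed correlations, significant in about 29% to 99% of trials if pooled and about 13% to 69% within one country, treating pupils as independent. If countries are pooled, country differences can add to this or cancel it.

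The documents do not support saying that the article will misread the coefficient as impact, or that an artefact of any given size will occur. The primary comparison between arms is unaffected. This is a secondary analysis worth correcting before results are seen.

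**What to change.** For any statement that links acceptability to later KAP:
- Among intervention pupils, model 9-month KAP on the matching acceptability score (OV KAP with MGO, STH KAP with MGLM), with baseline KAP and country as covariates. Cluster inference by school with a small-sample correction, since there are only about 9 intervention schools. Alternatively, use a partial Spearman controlling baseline KAP within country.
- Do not use a raw change score in place of this adjustment.
- Keep the raw Spearman and chi-square results as description by country only, and state which KAP time point they use.
- Call the adjusted result associational.

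The cost is analysis-plan wording, since every variable is already collected. The association will usually be smaller and, with so few schools, its interval wider. Adjustment removes the artefact only as far as the baseline score captures pupils' starting level.
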